# 1. Grant Mechanism

UCSF Department of Anesthesia and Perioperative Care Internal Funds - $18,569

UCSF Resource Allocation Program (RAP) - $29,969

The purpose of this pilot randomized trial is to determine the feasibility of e-cigarettes and telephone counselling (compared to transdermal nicotine replacement and telephone counselling) as a harm-reduction tool that may lead to increased smoking cessation in the perioperative setting in smokers presenting for elective surgery at the San Francisco Veterans Affairs Medical Center. Secondary outcomes include acceptability of e-cigarettes over transdermal nicotine replacement, length-of-stay in the post-anesthesia care unit, hospital length-of-stay, postoperative complications within the first 30-days, and smoking status 8-weeks after randomization. This pilot study is designed to provide the preliminary data necessary to plan and fund a larger-scale randomized clinical trial that will assess the utility of e-cigarettes in achieving smoking cessation perioperatively. Our ultimate goal is to add to the limited existing data on the safety and efficacy of e-cigarette use in smoking cessation, specifically in the perioperative setting where the risks of continued smoking are great and the motivation to stop is high.

7. Proposal

**Title:** A Pilot Randomized Controlled Clinical Trial - "**E**lectronic **N**icotine **D**elivery device (e-cigarette) for **perioperative** **smoking** cessation in veterans" (The END Perioperative Smoking Pilot Study)

## SPECIFIC AIMS:

It is well-known that smokers suffer more complications and higher risk of mortality after surgery than non-smokers[^1^](#_ENREF_1)^,^[^2^](#_ENREF_2). Despite this knowledge, it is unclear what clinicians can do to minimize this risk. Surgery represents a 'teachable moment' that might encourage smokers to engage in permanent cessation[^3^](#_ENREF_3). Several small trials have shown that smoking cessation interventions can increase smoking cessation and reduce postoperative complications, particularly wound-healing complications, which can have an absolute risk reduction of up to 25%[^4-7^](#_ENREF_4). Smoking cessation initiated in the perioperative period can also promote long-term smoking cessation[^7-9^](#_ENREF_7). Despite the benefits of comprehensive smoking cessation interventions including nicotine replacement therapy, current standard of care at the SFVAMC does not routinely include specific preoperative smoking cessation pharmacotherapy or counselling. Although there is an urgent need for more data, e-cigarettes have been proposed as an alternative to nicotine replacement therapy that are at least as effective for smoking cessation[^10^](#_ENREF_10), and may be more acceptable to some patients[^11^](#_ENREF_11).

The main hypothesis of this pilot study is that the use of e-cigarettes and telephone counselling, compared to telephone counselling and transdermal nicotine replacement, in the perioperative period results in increased smoking cessation on the day of surgery and at 8-weeks after randomization in smokers presenting for elective surgery. As secondary hypotheses, the study will also assess the acceptability of e-cigarettes versus nicotine patches, postoperative complications within the first 30-days, length-of-stay in the PACU and hospital length-of-stay. We will examine the above hypotheses through the following aims:

**» Aim 1) To determine how e-cigarettes plus counselling compare to transdermal nicotine replacement plus counselling for the achievement of smoking cessation, when introduced prior to elective surgery in veterans.**

We plan to carry-out a pilot randomized controlled trial with parallel design comparing e-cigarettes and telephone counselling with transdermal nicotine replacement and telephone counselling. Our primary outcome is smoking cessation on the day of surgery, as confirmed biochemically by exhaled carbon monoxide. Smoking reduction (self-reported cigarettes per day) of 50% or more and bedside spirometry readings will be assessed as secondary outcomes.

**» Aim 2) To determine the acceptability of e-cigarettes amongst veterans as an aid for smoking cessation and to determine the feasibility of recruitment, randomization, and follow-up procedures in preparation for large-scale trial.**

Through implementation of this pilot trial, we will determine the feasibility and acceptability of e-cigarettes for smoking cessation perioperatively in the veteran population and obtain the preliminary data necessary to run a larger trial on the effectiveness of e-cigarettes as a perioperative smoking cessation aid.

**» Aim 3) To determine the safety of e-cigarettes as a harm reduction strategy to achieve short-term perioperative smoking cessation.**

We plan to improve the overall knowledge of the safety of short-term e-cigarettes use through careful surveillance for adverse events and side effects.

**» Aim 4) To determine if e-cigarette use preoperatively is associated with a lower risk of complications postoperatively.**

We plan to measure the following secondary outcomes: postoperative complications and mortality within the first 30 days, post-anesthesia care unit (PACU) length-of-stay, and hospital length-of-stay. This will help us understand if e-cigarettes have the potential to be used for harm-reduction perioperatively.

## Background and Significance:

Importance of the problem: Cigarette smoking is known to increase the risk of complications in patients undergoing surgery[^12-15^](#_ENREF_12). Cigarette smoking is more prevalent in United States veterans than non-veterans, being reported by 25% of veterans surveyed in 2007, compared to 20% of non-veteran adults[^16^](#_ENREF_16). Veterans may face unique challenges in smoking cessation, given the perception that smoking was a normalized part of military life[^17^](#_ENREF_17) and the high rate of coexisting mental health disorders[^18^](#_ENREF_18). An analysis within the Veterans Affairs (VA) healthcare system showed that pulmonary complications, cardiovascular complications, and surgical site infections were mediators of smoking-associated mortality at 6-months and 1-year after elective surgery[^19^](#_ENREF_19). A systematic review has shown that preoperative smoking cessation therapy improves both short and long-term smoking cessation[^20^](#_ENREF_20). In fact, a surgical encounter with the healthcare system has been described as a “teachable moment” that may provide extra motivation for patients to permanently stop smoking. Despite this information, most anesthesiologists do not routinely offer smoking cessation advice to their patients[^21^](#_ENREF_21)^,^[^22^](#_ENREF_22).

Innovative nature of the proposed research: There is currently a desperate need for more data regarding the use of e-cigarettes and their role in smoking cessation interventions[^23^](#_ENREF_23). Despite the fact that the FDA has not approved any e-cigarettes for therapeutic use, e-cigarettes are widely marketed with cessation-related claims[^24^](#_ENREF_24) and have the potential to bridge the gap between smoking cigarettes and abstaining. The limited evidence we do have is that e-cigarettes are modestly effective, similar to transdermal nicotine replacement, in achieving smoking cessation at 6-months with few significant adverse events[^10^](#_ENREF_10). A review of e-cigarettes showed that only 4 clinical trials have examined the efficacy of e-cigarettes for smoking cessation, 3 of which did not have a control group[^24^](#_ENREF_24). Despite this paucity of data, a survey of 112 preoperative patients showed that 55% had tried e-cigarettes and 71% of those that had tried stated that their reason was to quit smoking[^25^](#_ENREF_25). The current study will attempt to determine the acceptability of e-cigarettes as a smoking cessation aid and add to the limited existing data on the safety and efficacy of e-cigarette use in smoking cessation, specifically in the perioperative setting where the risks of continued smoking are great and the motivation to stop is high.

Next steps and potential impact of findings: The findings from this study will demonstrate the feasibility and acceptability of e-cigarettes as a smoking cessation aid perioperatively, providing preliminary data that will allow for larger studies and improved understanding of the safety and efficacy of e-cigarette use, not only in the perioperative environment, but also more broadly in a public health context. Furthermore, current literature indicates that dual use of e-cigarettes and conventional cigarettes is common[^24^](#_ENREF_24) and may reduce the potential harm-reduction role e-cigarettes might play in the broader public health context, since light and intermittent smoking of conventional cigarettes still conveys a significant mortality risk compared to abstinence[^26^](#_ENREF_26). Previous studies of e-cigarette use for smoking cessation have not specifically counselled patients to refrain from dual use, so this study will contribute by determining how commonly dual use occurs in a controlled setting.

## Preliminary studies:

**Research Environment and Feasibility**: SFVAMC provides a unique environment to study smoking cessation initiated in a perioperative setting. Considering only surgical admissions at the SFVAMC in 2011, 21.9% had an International Classification of Diseases 9 (ICD-9) code of 305.1, indicating tobacco use during the year of surgery, which demonstrates the burden of tobacco addiction among veterans and supports the feasibility of our proposed research plan. These rates also highlight the relevance and importance of studying smoking cessation in the VA population. Furthermore, the surgical encounter is a time when veterans are engaged in healthcare and represents an opportune moment for a dedicated smoking cessation intervention. SFVAMC cares for almost 4000 surgical patients per year, making it an ideal site to study perioperative smoking cessation interventions.

**Ability to Implement Clinical Trials:** Our research team has extensive experience with clinical trials initiated during perioperative care[^4^](#_ENREF_4)^,^[^27-36^](#_ENREF_27). In particular, [name] has developed and implemented a randomized trial of a perioperative smoking cessation intervention[^4^](#_ENREF_4). [name] has extensive expertise in the development and implementation of clinical trial research protocols to reduce perioperative risk ([**www.betablockerprotocol.com**](http://www.betablockerprotocol.com)). [name] is a member of the UCSF Center for Tobacco Control Research and Education with interests in the health effects of environmental toxins, including smoking. These prior projects demonstrate the ability of our research team to develop protocols, test them in randomized controlled trials, implement them in hospital systems, and demonstrate safety and efficacy in routine clinical use.

## Detailed Experimental Design and Methods:

**Study Design:** Randomized controlled trial with 2 parallel arms:

1) Electronic nicotine delivery device group (ENDD) + referral to the California Smokers' Helpline

2) Control group (referral to the California Smokers' Helpline plus transdermal nicotine replacement)

**Study population:** Adults presenting for elective surgery at the SFVAMC.

**Identification of subjects:** Potential subjects will be identified on the basis of operating room bookings and current smoking history at their preadmission evaluation in the Anesthesia Preoperative Clinic (APO clinic). We will aim to recruit patients at least 1 week preoperatively, but accept patients up to 3 days preoperatively so as to maximize the number of available subjects, but allow enough time to begin smoking cessation preoperatively. They will be seen for further evaluation of inclusion and exclusion criteria at the time of their usual preoperative assessment in the APO clinic, which according to a recent quality improvement audit, was a median of 6 days preoperatively.

**Inclusion criteria:** adults (age >18), any gender, scheduled to undergo elective surgery at the SFVAMC. Daily smokers based on self-report of at least 2 cigarettes/day and having smoked in the last 7 days. Presenting to APO clinic at least 3 days preoperatively.

**Exclusion criteria:**

Emergency surgery (booked <24 hours preoperatively)

Consumers of non-cigarette forms of tobacco only (pipe, smokeless tobacco) or marijuana only

Already enrolled in a smoking cessation trial or current smoking cessation pharmacotherapy

Already daily users of e-cigarettes or previous adverse reaction to e-cigarette or transdermal nicotine

Poor proficiency of English language**¸**as indicated by need for an interpreter (including family members) at the preadmission visit

Lacking capacity for consent (e.g. due to mental illness or dementia)**,** as indicated by consent for surgery and other medical procedures being obtained from a substitute decision maker

Pregnant or breastfeeding

Unstable cardiac condition (unstable angina, unstable arrhythmia)

## Control and intervention groups:

**1) Electronic nicotine delivery device group (ENDD) + referral to the California Smokers' Helpline**

The ENDD group will receive:

i) 6-week supply of disposable "NJOY" ENDDs (e-cigarettes)

-the number of e-cigarettes will be determined by equating the number of e-cigarettes to the number of cigarettes smoked per day (1 pack per day = 2 e-cigarettes per day = 14 e-cigarettes/week)

-veterans will be given detailed instructions for use and also instructed to start with the high nicotine content (4.5%) strength for three weeks, then decrease to the low nicotine content (2.4%) for two weeks, then switch to nicotine-free for the final week

ii) referral to the California Smokers' Helpline

-the California Smokers' Helpline is a telephone helpline offering smoking cessation counselling 7am-9pm weekdays and 9am-5pm weekends. Counselling includes individualized counselling and quit plan development, strategies to prevent relapse, and follow-up calls.

iii) brief advice from the research assistant lasting less than 2 minutes, typically a few sentences such as the following:

“The most important advice I can give you is that quitting smoking is the number one thing you can do for your health. Quitting smoking before surgery may reduce complications around surgery and there’s evidence that the longer you quit before your surgery, the less complications you’ll have. That's why your surgeon and anesthesiologist have recommended that you stop smoking as soon as possible. I encourage you to make use of the resources that have been provided to you to help you quit and to set your quit date for as soon as possible.”

iv) a brochure from the American Society of Anesthesiologists (ASA) about quitting smoking before surgery (available free from the ASA).

**2) Control group (referral to the California Smokers' Helpline + transdermal nicotine replacement therapy)**

The control group will receive the same counselling as the intervention group, but will receive a prescription for transdermal NRT instead of ENDD:

A prescription for 6 weeks of transdermal nicotine replacement (on-formulary at the VA) in the following doses: For smokers of 10 cigarettes per day or more, a 3-week supply of 21 mg/d, 1-week supply of 14 mg/d, 1-week supply of 7 mg/d, and 1-week of 0mg/d. Smokers of <10 cigarettes per day, 3 weeks of 14 mg/d patches 2 weeks of 7 mg/d patches, and 1-week of 0mg/d.

As with the intervention group, the control group will receive:

i) referral to the California Smokers' Helpline, ii) brief advice lasting less than 2 minutes, iii) a brochure from the ASA about quitting smoking before surgery

Table 1. Summary of study intervention

| **Study intervention** | **Intervention group (ENDD)** | **Control group** |
| --- | --- | --- |
| E-cigarettes (6-weeks) | YES | × |
| Transdermal NRT (6-weeks) | × | YES |
| Referral to the California Smokers' Helpline telephone helpline | YES | YES |
| Brief advice | YES | YES |
| ASA brochure | YES | YES |

## Outcomes:

**Primary outcome:** Smoking status on the day of surgery (48-hour point-prevalence abstinence), by self-report and confirmed with exhaled carbon monoxide (CO), which normalizes (to <10 ppm) within 24 hours after smoking cessation and should not be elevated with e-cigarette use only.

**Secondary outcomes:**

1. Descriptive outcomes of proportion of veterans eligible for inclusion, reasons for exclusion, and proportion of eligible veterans consenting to participate. Acceptability outcomes of satisfaction and use of intervention (any versus continuous) 8-weeks after randomization.

2. Smoking status at 8-weeks after randomization, as confirmed by exhaled CO.

3. Smoking reduction on the day of surgery and at 8-weeks after randomization (defined as 50% or less of baseline cigarettes smoked per day). Dual use of e-cigarettes and conventional cigarettes will also be assessed.

4. Bedside spirometry FEV1 (forced expiratory volume in first second), FVC (forced vital capacity), and cotinine level at 8-weeks after randomization (compared to baseline).

5. Postoperative complications or mortality within 30-days (by telephone self-report + chart review)

6. PACU length-of-stay

7. Hospital length-of-stay

8. Long-term assessment at 6 months - self-reported smoking status, including dual use of e-cigarettes.

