## Randomization and blinding:

After collection of baseline data, randomization will be done by computer-generated scheme with randomly permuted block sizes of 3 or 6 in a 2:1 fashion. Allocation will be concealed by consecutively numbered, sealed, opaque envelopes. Due to the nature of the intervention, blinding of subjects is not possible. whenever possible, healthcare providers will be blinded throughout the perioperative period. However, patients may report being in the study to their providers, which may inadvertently cause unblinding. Outcome adjudicators will be blinded.

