## Statistical analysis plan:

Descriptive statistics to assess feasibility:

-proportion ineligible for inclusion (95% CI by bionmial exact) and reasons for exclusion

-proportion of eligible veterans declining to participate (95% CI by binomial exact)

Baseline characteristics to be collected prior to randomization: age, gender, race/ethnicity, comorbidities (hypertension, coronary artery disease, chronic obstructive pulmonary disease, diabetes mellitus, other cardiac disease), scheduled surgical procedure and subspecialty, smoking habits (number of cigarettes per day, years smoking), Fagerstrom score for nicotine dependence. Operative day information to be collected in addition to outcomes listed below: surgical procedure, duration of surgery, anesthesia type (local/monitored anesthesia care/regional/general/combined)

| **Outcome** | **Data Description** | **Likely Distribution** | **Hypothesis Test** |
| --- | --- | --- | --- |
| Smoking cessation (primary outcome) | Proportion | n/a | Fisher’s exact test |
| Smoking reduction | Proportion | n/a | Fisher’s exact test |
| Smoking amount | Cigarettes/day, Continuous  Median (IQR) | Normal or skewed (plot histogram) | Normal: two-sided t-test  Skewed:Wilcoxon rank-sum |
| Unanticipated hospital admission | Proportion | n/a | Fisher’s Exact Test |
| Hospital length of stay | Days  Continuous  Median (IQR) | Skewed | Time-to-event using Cox proportional hazards model; graph Kaplan-Meier plot |
| 8-weeks after randomization: Agreement to (0-7 likert) "I was satisfied with product I was given (e-cigarette or patch) to help me quit" (and similar questions regarding how helpful they found it, and whether they would recommend e-cig/patch) | Likert 0-7, Ordinal, Median (IQR) | Skewed | Wilcoxon rank-sum |
| 8-weeks after randomization: During the 6-weeks after you entered the study, how often did you use the product you were given (e-cigarettes or patch)?  Everyday, most days, a few times a week, once a week, less than once a week, did not use at all | Proportion that used everyday Proportion that did not use at all. | n/a | Fisher’s exact test |
| Change in FEV1, FVC, salivary cotinine | Liters, Continuous (Mean, SD) | Normal | Paired t-test |
| Composite of 30-day postoperative complications and mortality | Proportion | n/a | Fisher’s Exact Test |
| Duration in PACU | Hours  Continuous  Median (IQR) | Skewed | Time-to-event using Cox proportional hazards model; graph Kaplan-Meier plot |

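### The FEV1/FVC change spans the operation in an unrestricted elective case mix, and the paired t-test cannot separate operative loss in chest or upper-abdominal cases from an effect of quitting or of the product

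*Protocol*

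**What the plan says.** Protocol, Secondary outcomes, item 4, defines the endpoint: "Bedside spirometry FEV1 (forced expiratory volume in first second), FVC (forced vital capacity), and cotinine level at 8-weeks after randomization (compared to baseline"). Specific Aims places spirometry under Aim 1, the comparison of e-cigarettes with patches for achieving cessation.

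On timing, Randomization and blinding states: "After collection of baseline data, randomization will be done by computer-generated scheme with randomly permuted block sizes of 3 or 6 in a 2:1 fashion". No stratification by type of operation is described. Detailed Experimental Design and Methods says the preoperative clinic visit, according to a recent audit, "was a median of 6 days preoperatively". It requires "Presenting to APO clinic at least 3 days preoperatively" and sets no maximum interval.

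On case mix, the same section gives the population as "Adults presenting for elective surgery at the SFVAMC", and the inclusion criterion is "adults (age >18), any gender, scheduled to undergo elective surgery at the SFVAMC". The only exclusion by type of surgery is "Emergency surgery (booked <24 hours preoperatively").

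On analysis, the outcome table in the protocol's Statistical analysis plan section has a row "Change in FEV1, FVC, salivary cotinine", summarised as mean and SD, assumed normal, and tested with a paired t-test. The planned operation and its subspecialty are recorded before randomization, and the operation actually done and its duration are recorded on the day. None of these enters the spirometry row.

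**The concern.** Spirometry is offered as a smoking outcome, but an operation lies between its two readings. Where that operation is on the chest or upper abdomen, FEV1 and FVC may still be reduced at the second reading for reasons unrelated to smoking or to the study product.

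A paired t-test asks only whether the mean change differs from zero. An operative fall common to both arms goes straight into that mean, and nothing in the stated test removes it. A fall could be read as harm from the product, or a gain from quitting could be masked.

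The control group is 10 people, so a few such cases can move its mean noticeably. They would also strain the normality assumption in the table.

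**Working it through.** **The plan's own figures.** The protocol gives no spirometry effect, SD or power. Its only power figure, an effect size of 1.085, concerns the satisfaction scale. It reproduces under the two-sided normal approximation, (1.960 + 0.842) × √(1/10 + 1/20) = 1.085, but does not bear on this point.

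**Timing (protocol inputs).** Eight weeks is 56 days. At the median clinic interval the second reading falls 56 − 6 = 50 days after surgery. At the 3-day minimum it falls 56 − 3 = 53 days after. At these intervals the change spans the operation. It would not do so only for someone enrolled more than 8 weeks ahead, which the protocol does not rule out.

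**What follows is illustration.** The share of chest and upper-abdominal cases, the operative loss and the SD of change are assumptions.

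*Influence of single cases.* Shift in an arm mean = −d × k/n, with d = 0.3 to 0.7 L:

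| Affected cases | Shift in arm mean (L) |
|---|---|
| 1 of 10 controls | −0.03 to −0.07 |
| 2 of 10 controls | −0.06 to −0.14 |
| 1 of 20 e-cigarette participants | −0.015 to −0.035 |

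*Before-after test.* Let a share p of participants lose L litres on average, with no effect of smoking or product. The mean change shifts by −p × L: from −0.10 × 0.1 = −0.01 L to −0.30 × 0.6 = −0.18 L. Take an SD of change of 0.25 L in unaffected participants, and an overall SD of √(0.25² + L² × p(1 − p)). The noncentral t distribution then gives these approximate rejection rates for a nominal 5% test:

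| p | L (litres) | Shift (L) | n = 20 | n = 30 |
|---|---|---|---|---|
| 10% | 0.1 | −0.01 | 5.3% | 5.5% |
| 20% | 0.3 | −0.06 | 15.1% | 20.9% |
| 30% | 0.6 | −0.18 | 53.8% | 72.7% |

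Both sample sizes are shown because the row does not say whether the test runs on all 30 participants or within an arm.

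*Between-arm comparison.* The planned operation is fixed before allocation, so the expected operative shift is the same in both arms and the expected difference is 0. Imbalance in case mix adds an SD of L × √(p(1 − p)(1/20 + 1/10)) to the arm difference: 0.1 × √(0.09 × 0.15) = 0.012 L at the low end and 0.6 × √(0.21 × 0.15) = 0.106 L at the high end.

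The hypergeometric probability that the affected share differs between arms by at least 20 percentage points is about 3% with 3 such cases in 30, 14% with 6 and 20% with 9. An imbalance of 20 points would move the arm difference by 0.2 × L, which is 0.02 to 0.12 L.

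**The case against.** The strongest reply is that randomization already deals with this. Any operative fall has the same expected value in both arms, so pooling operations does not bias a comparison of arms. What remains is the noise and chance imbalance that any unstratified prognostic factor brings at 20 versus 10. This stands, and it locates the fault: the systematic shift comes from the paired test, not from the wide eligibility.

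Three stronger readings are tempting, and the documents support none of them.

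- A reader might infer that FEV1 and FVC here record the operation instead of smoking. The change mixes both, and the documents say nothing about the size or duration of operative loss at about 7 weeks, or about how many chest or upper-abdominal cases to expect. Such cases are merely not excluded.
- A reader might infer that one or two cases would decide the sign of an arm's mean. No cessation effect is given to compare with. If the SD is assumed to be 0.15 L, the standard error is 0.15/√10 = 0.047 L or 0.15/√20 = 0.034 L, so one case moves the mean by roughly 0.4 to 1.5 standard errors.
- A reader might infer that the SD handed to the full-scale trial is inflated. Mixing does raise it: with 10% affected and a 0.5 L fall, √(0.15² + 0.09 × 0.5²) = 0.21 L against 0.15 L. If the full trial enrols the same case mix, however, that is the right planning SD. The protocol also says the full trial will lean towards Aims 2 to 4, whereas spirometry sits under Aim 1.

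It can also be said that subgroup and sensitivity analyses belong in a separate analysis plan, which is not at hand. That is fair for the companion analysis. It does not excuse the test itself, which the protocol fixes.

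**Conclusion.** The point holds in a limited form. The spirometry change spans the operation at the stated intervals, no elective procedure is excluded by site, and the stated paired t-test cannot separate operative loss from an effect of quitting or of the product in chest and upper-abdominal cases. That much rests on the protocol's own text, together with the ordinary expectation that such operations can reduce a forced breath.

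The size is unknown. Under the assumed ranges the before-after mean could shift by as little as 0.01 L, which hardly matters, or by as much as 0.18 L, which would make the test uninterpretable. Compared between arms, the same data carry no expected shift, only extra variability and a possible chance imbalance.

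The stakes are low: this is one of eight secondary outcome items in a 30-person pilot that expects only rough estimates. It is worth correcting because the correction is cheap.

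**What to change.** In the outcome table, for FEV1 and FVC only (the argument does not extend to cotinine, which shares the row):

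1. Replace the paired t-test with a between-arm comparison of change, adjusted for the baseline value (for example ANCOVA), in all participants.
2. Pre-specify a companion analysis that leaves out participants whose planned procedure, as recorded before randomization, is thoracic or upper abdominal. Classifying by the planned procedure keeps the rule independent of allocation.
3. List the left-out participants' values individually, and report medians alongside means.
4. State that a within-arm before-after change will not be interpreted as a smoking or product effect.

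The cost is wording only: no new data or visits are needed, because the procedure is already collected at baseline. The companion analysis will have slightly fewer participants, which is why it accompanies the all-participant comparison and does not replace it.

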**Equipment & Supplies**

Bedfont Scientific piCO+ Smokerlyzer and MIR Spirobank Spirometer

The Smokerlyzer ($620) is used to detect exhaled carbon monoxide, which at levels <10ppm confirms abstinence for the previous 24 hours. The initial purchase includes 12 oval D-pieces that require changing once per month, 25 mouthpieces that require changing after each use, and 25 non-alcohol based disinfection wipes (alcohol-based wipes will damage the sensor). This study will also require 1 box (250) mouthpieces ($37) and 75 additional non-alcohol based disinfecting wipes ($45). The MIR Spirobank Spirometer ($525) and additional mouthpieces ($69) will be used to assess the secondary outcome of change in FEV1 and FVC.

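### At 8 weeks, smoking status rests on a 24-hour CO test alone, while cotinine is analysed only as a paired mean change that neither compares the arms nor separates quitting, cutting down and switching

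*Protocol*

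**What the plan says.** Four parts of the protocol bear on this point.

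- **8-week smoking status.** Secondary outcome 2 is "Smoking status at 8-weeks after randomization, as confirmed by exhaled CO". Under Equipment & Supplies the protocol gives the reach of that test: "which at levels <10ppm confirms abstinence for the previous 24 hours".
- **Cotinine.** Secondary outcome 4 places "cotinine level at 8-weeks after randomization (compared to baseline" beside FEV1 and FVC. The outcome table in the section Statistical analysis plan has one row for all three: "Change in FEV1, FVC, salivary cotinine | Liters, Continuous (Mean, SD) | Normal | Paired t-test". No cut-off, individual classification or between-arm comparison of cotinine is given.
- **End of study nicotine.** The e-cigarette arm starts with three weeks at the higher strength: "then decrease to the low nicotine content (2.4%) for two weeks, then switch to nicotine-free for the final week". Control participants smoking 10 or more cigarettes a day receive "a 3-week supply of 21 mg/d, 1-week supply of 14 mg/d, 1-week supply of 7 mg/d, and 1-week of 0mg/d"; lighter smokers have five weeks of active patches and then a week at zero.
- **Nicotine from other sources.** Dual use is to be assessed (secondary outcome 3). In the Qualitative Method section, the questions on same-day dual use and on e-cigarettes from outside the study are listed for the e-cigarette group only.

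**The concern.** A CO test with a 24-hour reach can be passed by someone who smokes intermittently and has skipped a day. That matters here because entry needs only 2 cigarettes a day, halving consumption is itself an outcome, and participants know their assignment. The cotinine sample from the same visit could show which self-reported quitters with a normal CO still carry nicotine that they have not reported. The plan does not use it in this way.

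The analysis that is planned tests whether participants differ from their own baseline. It does not test whether e-cigarettes differ from patches. Nor does it distinguish someone who stopped all nicotine from someone who smokes less, or someone who still smokes from someone who has moved fully to another nicotine source. The last distinction is central to a trial that presents e-cigarettes as harm reduction and promises to show how common dual use is.

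**Working it through.** **1. Budgeted samples.** The section on salivary cotinine costs gives 3 samples per subject at an assumed $33. 3 × 30 = 90 samples, and 90 × $33 = $2,970, which reproduces the protocol's figure. The outcomes name two time points, baseline and 8 weeks: 2 × 30 = 60 samples, or $1,980. The other 30 samples ($990) have no stated time or use. The protocol's only power statement concerns satisfaction and is not affected.

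**2. Timing.** Weeks of study nicotine, counted from randomization if taken as scheduled:
- e-cigarettes: 3 + 2 = 5, then 1 nicotine-free week
- patches, 10 or more cigarettes a day: 3 + 1 + 1 = 5, then 1 week at zero
- patches, under 10 a day: 3 + 2 = 5, then 1 week at zero

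The 8-week visit is therefore 8 − 5 = 3 weeks (504 h) after the last scheduled nicotine. The protocol gives no cotinine half-life, so I assume 12 to 48 h. The share remaining is 0.5^(hours ÷ half-life):
- 504 h: 0.5^(504/48) = 0.07% at the slow end, and effectively nil at 12 h
- 336 h (2 weeks, if nicotine ran to the end of week 6): 0.5^(336/48) = 0.8% at the slow end

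Study product used on schedule would not explain a raised value at 8 weeks.

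**3. What the paired mean can show.** As an illustration, set baseline cotinine at 100, let quitters fall to 0 and let all others stay unchanged. With 20 and 10 participants, the pooled mean change is −100 × (20 × qE + 10 × qC) ÷ 30, where qE and qC are the quit rates in the e-cigarette and control arms.
- 50% and 50%: −100 × (10 + 5) ÷ 30 = −50
- 25% and 100%: −100 × (5 + 10) ÷ 30 = −50
- 75% and 0%: −100 × (15 + 0) ÷ 30 = −50
- everyone halves intake and nobody quits: −50

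If pooled, the result is the same whether the arms are equal or far apart in either direction. Running the test within each arm removes that problem but leaves another: in the e-cigarette arm, −50 can mean 10 of 20 stopped or all 20 halved. A participant who gives up cigarettes but keeps the same nicotine intake from another product contributes 0, exactly like a continuing smoker.

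**4. Scale.** One participant is 1/20 = 5 percentage points in the e-cigarette arm and 1/10 = 10 in the control arm. The protocol states no expected 8-week quit rate, cotinine cut-off or cotinine standard deviation, so the number who would change class cannot be derived.

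**The case against.** The strongest reply is that CO was chosen on purpose. The outcome is smoking, not nicotine use, and the primary outcome definition notes that e-cigarettes alone should not raise CO. Cotinine cannot tell a cigarette from an e-cigarette, so it would be a poor main check in this trial. That stands, and CO should stay.

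A reader might infer several stronger points that the documents do not support:
- **That a raised 8-week cotinine proves smoking.** The three-week gap holds for the schedule only. The use question allows for anything from daily use to none, so study product may be left over, and the protocol itself asks about products from elsewhere.
- **That the mean change cannot be interpreted, or that the samples are wasted.** The mean estimates change in nicotine exposure, a sensible companion to spirometry, and the individual values are collected in any case.
- **That the arms are pooled.** The table does not say.
- **That the 8-week quit rate is wrong by a known amount, or biased between arms.** No figure in the protocol supports either.

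It can also be said that a supplementary classification is normally left to a separate analysis plan. That would carry weight if the protocol were silent. Here its own outcome table fixes the cotinine analysis, with a unit that cannot apply to cotinine and a test that makes no between-arm comparison.

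**Conclusion.** The point holds in a limited form. At 8 weeks the only confirmation of smoking status reaches back about 24 hours. Cotinine from the same visit, about 3 weeks after the last scheduled study nicotine, is confined to a paired mean change in the wrong unit. That analysis does not compare the arms, leaves open whether they are pooled, and cannot separate quitters, reducers and people who switched products.

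The timing rests on product being used as scheduled from randomization and on the assumed half-life. The size of any change to the quit rate is unknown. This concerns secondary outcomes in a 30-person pilot; the primary outcome and sample size are untouched. It is worth correcting because the pilot is meant to supply estimates for the full trial and the correction needs no further assays.

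**What to change.** 1. Keep CO as the main confirmation of 8-week smoking status.
2. Keep the mean cotinine change, but give cotinine its own row with a concentration unit. Report the change by arm, with the between-arm difference and its confidence interval.
3. Add a supplementary 8-week table by arm, using a laboratory cut-off stated in advance:
   - *smoking*: reported smoking, or CO of 10 ppm or more
   - *cigarette-abstinent with nicotine use*: CO below 10 ppm and current nicotine use reported, including leftover study product
   - *nicotine-abstinent*: CO below 10 ppm, no nicotine use reported, cotinine below the cut-off
   - *not confirmed*: CO below 10 ppm, no nicotine use reported, cotinine above the cut-off

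   Show missing cotinine separately. As a sensitivity analysis of the 8-week quit rate, count the not-confirmed group as not quit.
4. Ask both arms at 8 weeks about all nicotine products currently used.
5. State the time and purpose of the third budgeted sample.

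Cost: protocol wording, one question and one table. The 60 samples needed lie within the 90 budgeted, although the price per sample is still an assumption in the protocol. The cells will be small, the split between the second and fourth classes depends on self-reported product use, and the confirmed quit rate may come out slightly lower.
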